## **15. Data collection and storage**

### **15.1. Data collection**

The Case Report Forms (CRFs) to be used in this study and the submission deadlines are as follows. In principle, all CRFs below should be sent by mail. All CRFs should be sent to the data center.

- (1) Basic subject data: Promptly after registration
- (2) Anticancer Drug Administration Record Form: At the time of discontinuation of treatment/within 2 weeks after completion
- (3) Treatment Termination Report Form: At the time of discontinuation of treatment/within 2 weeks after completion
- (4) Follow-up: Every 1 year or upon confirmation of recurrence
- (5) Blood tests, abnormal subjective and objective findings, abnormal values, etc.: At the time of discontinuation of treatment/within 2 weeks after completion
- (6) Tracking Report Form: At the time of request of the secretariat

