### **7.2. Follow-up for subjects who discontinued the study**

If any of the treatment discontinuation criteria are met, protocol treatment should be discontinued, and the timing, reason, and progress should be recorded in the “case report form” and evaluated up to the point of discontinuation. In addition, follow-up of adverse events should be conducted in discontinued cases until 4 weeks (day 28) after the last administration of S-1, or until the adverse events that may have been caused by the drug disappear, resolve, stabilize, or the laboratory values return to normal or stabilize.

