### 11. Observation/test items and timing

#### 11.1. Definition of treatment period

The treatment period for each subject is from the date of enrollment until 4 weeks after the last dose or until the start of post-treatment within 4 weeks of the last dose.

The principal investigator or a research associate investigator will investigate and confirm the following information prior to enrollment and initiation of administration

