#### 11.4. Endpoints during treatment period

Evaluate various test items and the subject’s condition.

- |                                       |                        |
|---------------------------------------|------------------------|
| 1) General condition:                 | PS, weight measurement |
| 2) Subjective and objective symptoms: | Same as 11.3 (2)       |
| 3) General blood/biochemistry/gas:    | Same as 11.3.(3)       |

- 4) Observation of targeted lesions: Same as 11.3.(4)  
 5) Tumor markers: Same as 11.3.(5)  
 6) Urinalysis: Same as 11.3.(6)

| Item/Period                                           | Before the start of treatment | During treatment (every 1–2 weeks)                | At the end of treatment |
|-------------------------------------------------------|-------------------------------|---------------------------------------------------|-------------------------|
| Patient background                                    | ○                             |                                                   |                         |
| Subjective and objective findings and PS              | ○                             | ○                                                 | ○                       |
| Target lesion observation (Search for new lesions)    | ○                             | In principle, every 2 months (Enforced as needed) | ○                       |
| General blood/biochemistry/gas and weight measurement | ○                             | ○                                                 | ○                       |
| Tumor marker                                          | ○                             | In principle, every 1 month*                      | ○                       |
| Urinalysis                                            | ○                             | as necessary                                      | as necessary            |

If any adverse events occur, they should be treated as often as possible to allow adequate observation of their progress (e.g., most abnormal, date of recovery or lightening), even if they occur on days other than those specified in all the above items.

\*This will be performed within the scope of insurance coverage.

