#### 11.5. After discontinuation/termination of drug administration

After discontinuation/termination of treatment to a total of 2 years after the first administration

As a rule, an examination and chest X-ray should be performed every 3 months. Imaging tests including chest CT, tumor markers (CEA, CYFRA) every 3 to 6 months, and blood tests (hemoglobin, white blood cell count and fraction, platelet count, Alb, T-Bil, AST, ALT, LDH, BUN, Cr, Na, K, Cl, Ca) as necessary.

After discontinuation/termination of treatment to a total of 3 to 5 years after the first administration

As a rule, an examination and chest X-ray should be performed every 6 months. Imaging tests including chest CT, tumor markers (CEA, CYFRA) every 6 to 12 months, and blood tests (hemoglobin, white blood cell count and fraction, platelet count, Alb, T-Bil, AST, ALT, LDH, BUN, Cr, Na, K, Cl, Ca) as necessary.

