#### Percentage of occurring adverse events (adverse reactions)

Using all treated cases as the denominator and the incidence of adverse events judged to be caused by the study treatment as the numerator, the proportion of the worst grade in the entire course according to the CTCAE v4.0 of the Japanese translation JCOG version is determined.

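### The safety form in Protocol 15.1(5) falls due before the 4-week post-dose adverse-event period ends, no later safety form is named, and the visit schedule for those weeks is inconsistent

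*Protocol*

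**What the plan says.** **Follow-up period.** Protocol 7.2 states that "follow-up of adverse events should be conducted in discontinued cases until 4 weeks (day 28) after the last administration of S-1", or until possibly drug-related events have resolved or stabilised. The sentence before it says that such patients are "evaluated up to the point of discontinuation". Section 7.2 names discontinued patients only. For everyone else the period comes from 11.1: "The treatment period for each subject is from the date of enrollment until 4 weeks after the last dose", closing earlier if post-treatment begins within those weeks.

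**Endpoint.** Section 12.2 defines the adverse-event endpoint, among all treated patients and for events judged caused by study treatment, as "the proportion of the worst grade in the entire course".

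**Form.** Item (5) of 15.1 is the only listed form that names blood tests and symptoms. Its deadline is: "Blood tests, abnormal subjective and objective findings, abnormal values, etc.: At the time of discontinuation of treatment/within 2 weeks after completion". Two forms can follow. One is a follow-up form, yearly or at confirmed recurrence. The other is a tracking form when the secretariat asks for it. Neither is described as carrying adverse-event data.

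**Visits.** The table in 11.4, the section on the treatment period, schedules symptoms, performance status, weight and blood tests every 1–2 weeks. Section 11.5, which begins once the drug is stopped, says: "As a rule, an examination and chest X-ray should be performed every 3 months". Blood tests there are done only if needed.

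**Monitoring.** Section 17 describes central monitoring from submitted case report forms, with no site visits and no check against source documents.

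**The concern.** The period over which toxicity is to be observed and the date on which toxicity is to be reported do not match. A site that sends the form on time sends it before the observation period is over, and the protocol does not ask for an update. An event that first appears, or reaches its worst grade, after the form has gone has no routine way into the database. Monitoring as described in section 17 would not find it.

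Adverse-event rate and severity is a secondary endpoint. Toxicity is also one of the seven considerations in 13.4(3) for choosing an arm when one arm's completion rate exceeds 40% and the two rates differ by no more than 15 points. If sites read the deadline differently, or some amend their forms and others do not, worst grade will cover different lengths of time in different patients.

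**Working it through.** The plan gives no figure to reproduce here. The check is calendar arithmetic on its own time points.

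**Inputs**
- Post-dose period: 28 days (7.2 for discontinued patients, 11.1 for all).
- *g*, the time allowed for the form after treatment is declared ended. The slash in 15.1(5) can be read in two ways. On the literal reading, *g* = 0 for discontinuation and 14 for completion. On the shared reading, *g* = 14 for both.
- *d*, the days from the last dose to the date treatment is declared ended. The protocol does not fix *d*. It is 0 if the end is declared on the last dosing day, 7 for an Arm B patient stopped at a scheduled course start after the rest week, and about 28 for a patient stopped under 7.1(1) or (2).

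**Formula.** Days of the period after the form's deadline = max(0, 28 − *d* − *g*).

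| Situation | *d* | Literal reading | Shared reading |
|---|---|---|---|
| Completed, declared on last dosing day | 0 | 28 − 0 − 14 = 14 (50%) | 14 (50%) |
| Discontinued on last dosing day | 0 | 28 − 0 − 0 = 28 (100%) | 28 − 0 − 14 = 14 (50%) |
| Arm B, stopped at a course start | 7 | 28 − 7 − 0 = 21 (75%) | 28 − 7 − 14 = 7 (25%) |
| Stopped under the 28-day rule | 28 | 0 | 0 |

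A form sent before its deadline leaves more days uncovered. With a deadline on or after day 28 from the last dose, every cell is 0.

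**Visits in the same 28 days.** Read together, 11.1 and 11.4 continue assessments every 1–2 weeks to day 28. If 11.5 governs from the day the drug stops, the first routine examination is at about 365.25 / 4 ≈ day 91, which is 91 − 28 = 63 days after the period has closed. The two readings cannot both apply. Even on the first, the form is due before the last of those assessments.

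**What other routes capture.** Sections 10.1 and 10.2 separately require reports of deaths within 30 days of the last treatment, later deaths possibly caused by treatment, Grade 4 non-hematologic toxicity, unexpected Grade 3 events, lasting impairment and other events judged important. That leaves Grade 1–2 events, expected Grade 3 events and expected hematologic toxicity without another routine route.

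**The case against.** The strongest reply is that a submission deadline is not a data cut-off. Section 7.2 requires follow-up to day 28, 11.4 asks for extra observation whenever an event occurs, the secretariat can request a tracking form, and the gravest events have their own reports. The form itself is not shown and may have room for later entries. This stands to the extent that the late data cannot be called lost. They may go unrecorded, and only in the categories outside 10.1 and 10.2. It does not remove the mismatch, because no document asks the site to update a form already sent.

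Three stronger conclusions are tempting and are not supported:

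- **No contact occurs until 3 months.** This uses 11.5 alone. Sections 11.1 and 11.4 can be read as keeping 1–2-weekly visits to day 28, for completers as well. What the text shows is a conflict between sections.
- **Early stoppers lose most, so the arm with more stopping looks safer.** This needs the literal reading of the slash; on the shared reading, discontinuers and completers declared on the last dosing day both have 14 days uncovered. It also overlooks that toxicity often leads first to suspension or postponement. Patients who then cannot restart are stopped at about day 28 and lose nothing.
- **The planning completion rates of 55% and 40% mean that 45% and 60% of patients are affected.** Completion in 12.2 also requires at least 70% of the planned dose, so a non-completer need not have discontinued. Patients who stop for recurrence are excluded from that rate. The share of patients affected is not in the document.

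It is also fair to say that the toxicity which causes a stop can be recorded at the stop, and that the protocol gives no figure for how often the worst grade comes later.

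**Conclusion.** The point holds in a limited form. On either reading of 15.1(5), the safety form can fall due before the period in 7.2 and 11.1 has ended, and no later safety form is named. For treatment declared ended on the last dosing day, 14 of the 28 days fall after the deadline, rising to 28 for a discontinued patient on the literal reading. For patients stopped under the 28-day rule the number is zero. These counts assume that the form is sent on its deadline and is not amended afterwards.

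The consequence is possible under-recording of late or worsening Grade 1–2, expected Grade 3 and expected hematologic events, in an endpoint defined over the entire course. A reader might go on to infer a bias favouring one arm. The document supports neither its size nor its direction. The inconsistent visit schedule for the same weeks is a separate defect in the text and needs its own reconciliation. The point merits a change because the correction is specific and cheap and toxicity feeds the decision in 13.4(3).

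**What to change.** - Make the 15.1(5) form due after day 28 from the last dose, for example within 2 weeks of day 28. Alternatively, keep the present deadline and add a day-28 update page for all treated patients, completers included.
- Remove the ambiguity of the slash by stating the deadline separately for discontinuation and for completion.
- State that worst grade is computed over the same window in both arms.
- Reconcile 7.2 (including its phrase "evaluated up to the point of discontinuation"), 11.1, 11.4, 11.5 and 15.1, so that one visit schedule and one follow-up rule apply to the 4 weeks after the last dose.

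**Cost.** With the later deadline, forms would be due by day 28 + 14 = 42 instead of day 14, about 4 weeks later (up to 6 weeks later where the form is now due on the day of discontinuation). With an update page, the first form keeps its date and each patient adds one page. No sample-size or power figure changes.

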### **15.2. Preservation of records**

Records shall be kept at the data center in accordance with the “Standard Procedures” for record keeping, and documents and records related to the study shall be kept at the data center. The retention period shall be 5 years after the date of the report of the completion of the study or 3 years after the date of the final publication of the results of the study, whichever is later. Patient consent records, data related to the preparation of reports (e.g., laboratory data), IRB/IEC approval forms, and records and documents prepared at participating institutions will be retained by the investigator. The retention period will be 5 years from the date of the report of the completion of the study or 3 years from the date of the final publication of the results of the study, whichever is later.

## **16. Ethical matters**

### **16.1. Protection of subjects**

All researchers involved in this research will conduct the research in compliance with the “Declaration of Helsinki” and the “Clinical Research Act”. When handling information related to the implementation of the research, we will assign a research subject code unique to the research and give due consideration to the protection of the confidentiality of the research subjects. When publishing the results of the research, information that can immediately identify the research subjects, such as names and dates of birth, will not be included. In addition, information on research subjects obtained in the research will not be used for any purpose other than the purpose of the research.

### **16.2. Consent obtained**

Prior to enrolling subjects, the attending physician will provide a thorough explanation of the following items using the consent document. The subject will be given the opportunity to ask questions and sufficient time to decide whether to participate in the study. After confirming that the subject fully understands the study, the subject’s free and voluntary consent to participate will be obtained in writing. The attending physician will promptly hand a copy of the signed consent document to the subject. The original consent document will be kept in the medical record. The period of retention will be 5 years after the date of the report of the completion of the study or 3 years after the date of the final publication of the study, whichever is later.

### **16.3. Explanation**

- 1) Background, 2) Purpose of this study, 3) Method/content of treatment in this clinical trial, 4) Expected medical contribution, 5) Duration of this study, 6) Number of expected

participants in this study/place of study, 7) Expected effects and side effects, 8) Other effective treatment methods, 9) Samples used in the study, 10) If your health is harmed; 11) Free and voluntary consent; 12) If new significant information is obtained; 13) Possibility of discontinuation during the clinical trial; 14) Protection of personal information, protection of human rights, and disclosure of research results; 15) Things you should be aware of; 16) Your responsibility for the cost of treatment; 17) research funding, conflicts of interest, and research benefits; 18) benefits, disadvantages, and risks you may receive if you participate in this study; 19) secondary use of data; 20) contact information

#### **16.4. Privacy protection and subject identification**

Identification and matching of registered patients will be performed using the registration number issued at the time of registration, and the names of registered patients will not be shared with other facilities. In addition, patient names, medical record numbers, and other personally identifiable information will not be registered with the secretariat. Although the possibility of leakage of personal information cannot be completely eliminated, physicians participating in this study will make their utmost efforts to protect personal information in light of the possible risks.

#### **16.5. Compliance with protocols**

Investigators participating in this study will comply with this study protocol to the extent that patient safety and human rights are not compromised.

#### **16.6. Approval of Institutional Review Board (IRB) or Ethics Review Board**

Upon approval by the IRB or Ethics Review Board, the principal investigator at each institution will send a copy of the approval letter to the research secretariat. The original approval letter will be retained by the institution and a copy will be retained by the research secretariat.

#### **16.7. Changes in protocol content**

##### Classification of change in protocol content

In the event of a change in protocol content, a "Protocol Revision Application" must be submitted to the Data and Safety Monitoring Committee for approval prior to implementation of the change.

Changes in protocol content are divided into two types: amendments and revisions. The distinction between amendments and revisions is made by the Data and Safety Monitoring Committee members. Supplemental explanatory notes that do not fall under the category of changes in protocol content are distinguished as memorandums.

- (1) Amendment: Partial changes that may increase the risk to patients participating in the study or with respect to the primary endpoint.
- (2) Revision: Changes that are not likely to increase the risk to patients participating in the study and are not related to the primary endpoint.
- (3) Memorandum/Memorandum of Understanding: A supplement to the protocol distributed by the principal investigator/research secretariat to study personnel, not to change the content, but to unify variations in interpretation of the text, especially to call attention to them, etc.

##### Institutional IRB or Ethics Review Board approval at the time of protocol amendment/revision

If any amendments are made to the study protocol or patient instructions with the approval of the Data and Safety Monitoring Committee members during the study, the amended study protocol or patient instructions must be approved by the IRB or Ethics Review Board at each site.

If the content change is a revision rather than an amendment, it is up to each institution to determine whether it requires approval review by its IRB or Ethics Review Board.

Upon IRB or Ethics Review Board approval of the amendment, the principal investigator at each site will send a copy of the approval letter to the research secretariat. The original approval letter will be retained by the institution and a copy will be retained by the secretariat.

#### **16.8. Changes in the contents of the case report form (CRF)**

If, after the start of the study, the CRF is found to be incomplete, such as missing required data items or inappropriate categorization, etc., as long as it is determined that the scope of data collected does not exceed that specified in the “Observation, Examination, and Evaluation Items and Schedule” section, and the modification of the CRF will not increase the medical and financial burden on enrolled patients The CRF will be revised upon agreement between the Data and Safety Monitoring Committee and the research secretariat. The reporting of CRF amendments to the head of the medical institution and the application for revision of the CRF shall be in accordance with the regulations of the institution.

#### **16.9. Secondary use of data**

For data obtained in this study, there may be secondary use of data (e.g., meta-analysis) in a form that is not linked to personally identifiable information.

## **17. Monitoring and auditing**

Monitoring will be conducted as necessary, led by the research secretariat/principal investigator, to ensure that the study is being conducted safely and according to protocol and that data are being collected accurately. The CRF is prepared by the principal investigator/associate investigator or CRC (clinical research coordinator). Monitoring will be conducted centrally based on the data entered in the CRF collected at the research secretariat, and will not include site visits for site monitoring, including cross-checking with source documents. No directly identifiable patient information will be entered into the database of the secretariat. Maximum care will be taken to ensure that personal information is strictly protected.

### **17.1. Monitoring items**

Accumulation achieved, patient appropriateness, percentage of treatment completed, protocol treatment/completion status, serious adverse events, adverse reactions/adverse events, protocol deviations, and other issues related to study progress and safety.

### **17.2. Deviation from protocol**

- (1) Violation: As a rule, a “violation” is defined as any deviation from the protocol provisions that falls under more than one of the following items.
  - (1) affects the primary endpoint, (2) is caused by the physician/institution, (3) is intentional or systematic, (4) the degree of risk or deviation is extreme, or (5) is clinically inappropriate.
- (2) Deviations: Deviations that do not fall under either violations or tolerances. If many specific deviations are found, they shall be noted in the publication of the test results.
- (3) Acceptable scope: To be determined in advance between the research group and the research secretariat.

## **18. Costs and compensation**

Since S-1 used in this study is already covered by insurance for non-small cell lung cancer, the cost of the treatment will be covered by the regular insurance reimbursement. Any adverse health effects resulting from the study treatment will be handled under general medical care and will be borne partially by the subject, as with insurance treatment. No special compensation will be provided for hospitalization or transportation costs. It is recommended that physicians participating in the study obtain medical liability insurance.

